### Ethics Approval

This study is authorized by The Danish Medicines Agency and The Danish Health Research Ethics Committee and registered at Clinical Trials in the European Union (EU CT 2023-510187-13-00).

### Ethical Considerations

All pharmacological side effects will be handled in accordance with the Danish legislation. No risk or unknown side effects are expected from urotherapy, medical treatment, or withdrawal. No risks are expected by clinical examination and paraclinical measurements. The therapeutic potential for future patients justifies the project to be performed. Participation in this study will not lead to any disadvantages for the patient in their treatment. This study will be conducted in accordance with the protocol, applicable regulatory requirements according to Good Clinical Practice, and the ethical principles of the Declaration of Helsinki. Information regarding the participants is protected and anonymized according to the General Data Protection Regulation and the actual law. The study participants and their families will not be economically compensated for participating in this study; however, study medication costs will be covered throughout the entire study period.

### Safety Evaluations

Safety evaluations include AE, SAE, and SUSAR monitoring, registration of side effects as reported in the product summary, blood pressure, pulse, ultrasound-assessed PVR, and identification of urinary tract infection by urine dipstick and verified by routine urine cultivation and electrocardiogram. The listed safety parameters, except electrocardiograms, will be monitored at every visit during the study treatment administration, and urine dipstick will be performed at visit 2 and 3 if a participant reports symptoms of a urinary tract infection. Electrocardiograms will be monitored at baseline and at visit 2. The children and their parents will be asked for possible side effects at every visit and will always be able to contact a medical doctor or an investigator when a side effect is suspected. All participating children will be provided with a trial card on which the investigational product, trial number, investigator’s name, and a 24-hour emergency contact number are stated.

## Results

The BeDry study was approved by Clinical Trials in the European Union on June 12, 2024. Recruitment began on June 27, 2024, and will continue until 236 patients are included, which is expected to occur by September 2026. As of April 2025, 75 participants are included. The results will be submitted to Clinical Trials in the European Union and ClinicalTrials.gov within 1 year after the end of the trial.

## Discussion

### Anticipated Findings and Importance of This Research

Solifenacin is approved for the treatment of neurogenic detrusor overactivity in children and adolescents aged 2-18 years [17,18]. Though not approved for the treatment of idiopathic OAB in children, solifenacin is widely used off-label. The efficacy of solifenacin was found superior to placebo in terms of average voided volume per miction, daily maximum voided volume, and micturition frequency adjusted for total voided volume [11]. The efficacy of solifenacin by decreasing number of incontinence episodes per day was demonstrated by non–placebo-controlled prospective studies [19,20]. The safety and tolerability of solifenacin were found to be high, also by long-term use [12]. Predominantly, side effects such as xerostomia, constipation, blurred vision, headache, and fatigue were reported [11,19,20]. A few participants experienced more severe side effects, encompassing QT prolongation, severe constipation, fecal incontinence, and aggressive behavior, some of whom withdrew from the study due to the intolerable side effects and for safety reasons.

Mirabegron has been approved as an alternative to antimuscarinics in children with neurogenic detrusor overactivity [21]. In the pediatric population, mirabegron is used off-label in children with OAB, either as monotherapy or in combination with antimuscarinics [13,14]. The efficacy of mirabegron compared to that of placebo has been elucidated among children [10]. Furthermore, mirabegron has high safety and tolerability in the pediatric population [22]. Reported side effects [22] were blurred vision, constipation, abdominal cramps, and these were transient. No additional risk to the study participants is anticipated with the use of solifenacin and mirabegron.

A favorable safety profile was observed. In adult populations, the efficacy benefits of solifenacin and mirabegron outweigh the risks. This favorable benefit-risk ratio supports the further development of solifenacin and mirabegron in the treatment of pediatric populations with DUI.

With our protocol, we aim to investigate if treatment with a combination of solifenacin and mirabegron in low dose is effective in the reduction of DUI episodes over an 18-week treatment period compared to baseline and if combination therapy in low dose is superior to maximum dose of either solifenacin or mirabegron in children with noncomplete response to urotherapy and low dose monotherapy of solifenacin or mirabegron.

The results from our study will ensure evidence-based knowledge about the off-label treatment approach. By optimizing the stepwise medical treatment approach, the treatment can be shortened, side effects can be diminished, and unnecessary medical expenses can be minimized for individual families and the society both nationally and internationally.

Compared to experience from daily practice, randomized controlled trials allow for the systematic evaluation of both the safety and efficacy of treatments. This is crucial in pediatrics, where considerations such as appropriate dosing, potential side effects, and long-term outcomes need to be carefully assessed to ensure the well-being of children receiving treatment.

### Strengths and Limitations

The strengths of our study are the randomized single-blinded and controlled design with multicenter inclusion at 5 pediatric departments in Denmark. The investigators are blinded, and the participants know the treatment. This could cause a possible risk of affecting the final outcome of the study. Hence, no placebo effect is introduced. With single blinding, the investigators are not biased while treating the patients nor when interpretating data.

This study is embedded into daily clinical practice and reflects standard practice in many aspects other than randomization and collection of data. Usually, mirabegron is add-on pharmacotherapy if anticholinergics are not fully effective in treating DUI. The pragmatic design ensures timely inclusion of patients and reflects daily clinical practice where pharmacotherapy is initiated after inadequate effects of urotherapy.

The main limitation is compliance to the study medication over 18 weeks. We aim to reduce this risk by early termination of children with severe compliance issues (as <50%) during the treatment period. Compliance to the study medication is determined by counting the remaining tablets in the containers at each visit. This is performed by an unblinded nurse.

The risk of unblinding the blinded investigators is present, but we expect to reduce the risk by introducing unblinded study staff as project nurses, as well as the participants and their parents are instructed to not inform the investigator about the medication. Another limitation is the fixed dose of the combination therapy, thereby introducing a potential risk of undertreating the children allocated to the intervention group.

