### Withdrawal of Participants and Criteria for Discontinuation of Study

A study participant should be withdrawn from the study if at any time one of the following criteria is met:

It is the wish of the participant (or their parents/legally acceptable representative) for any reason (withdrawal of informed consent).The discretion of the investigator for safety or behavioral reasons.Severe noncompliance with protocol as judged by the investigator.The investigator judges it necessary due to medical reasons.Female participants who become pregnant should immediately discontinue study drug administration and will be discontinued from the study (female participants with childbearing potential are excluded from the study).The participant experiences adverse reactions, which endanger the health of the participant, require emergency treatment, are incompatible with the continuation of the study, or are expected to influence the results of the study.Participants with a condition or a situation that, in the investigator’s opinion, may put the participant at significant risk or may interfere significantly with the participant’s participation in the study will be discontinued from the study.Participant with any other condition or situation that in the investigator’s opinion may be valid for discontinuation from the study.

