### Primary End Point

The primary end point measure is treatment response assessed by change from visit 2 to end of study, according to the number of wet days per 7 days by DryPie.

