### Procedures During Pharmacotherapy

The participant timeline is illustrated in Table 1.

**Table 1 table1:** Schedule of the assessments.

	Visit 1: baseline	Visit 2	Visit 3: end of study or premature discontinuation
Weeks (days)	0	6 (42)	18 (126)
Visit scheduling window (days)		(SD 5)	(SD 5)
Informed consent	✔		
Inclusion and exclusion criteria	✔		
Background information including demographics	✔		
Registration of concomitant medication	✔	✔	✔
Urotherapy	✔	✔	✔
Randomization	✔		
Dispensation of study medication	✔	✔	
Compliance		✔	✔
Drug accountability		✔	✔
Registration of side effects as reported in the product summary		✔	✔
Registration of adverse events/serious adverse events/suspected unexpected serious adverse reaction		✔	✔
Clinical examination	✔		
Weight and height	✔		
DryPie	✔	✔	✔
48-hour frequency-volume chart	✔	✔	✔
Bower Visual Analog Scale Urgency	✔	✔	✔
Uroflowmetry	✔		✔
Postvoid residual urine	✔	✔	✔
Blood pressure and pulse	✔	✔	✔
Electrocardiogram	✔	✔	
Urine dipstick test	✔	(✔)^a^	(✔)^a^
Pediatric Incontinence Questionnaire	✔		✔
World Health Organization-Five Well-Being Index	✔		✔

^a^Performed in case of symptoms of urinary tract infection.

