### Sample Size

The estimates for the sample size calculations are based on 1 placebo-controlled trial, prospective studies, and retrospective studies [10-12,14,16]. We expect 15% of the children to have a complete response to treatment with low dose solifenacin 5 mg and 15% of the children to have a complete response to treatment with low dose mirabegron 25 mg. Of the remaining children (100% – 15% = 85%) who are noncomplete responders to low dose monotherapy, we expect 20% to have complete response to solifenacin 10 mg, 20% to have complete response with mirabegron 50 mg, and 50% to have complete response to combination therapy (solifenacin and mirabegron).

With the abovementioned estimations, we assessed a proportion of 32% (15% with complete response to solifenacin 5 mg + 85% noncomplete responders to low dose monotherapy solifenacin 5 mg × 20% with complete response to solifenacin 10 mg) of the participants randomized to solifenacin 10 mg will have a complete response. In addition, we assessed a proportion of 57.5% of the participants randomized to solifenacin 5 mg and mirabegron 25 mg. The sample size calculation was based on solifenacin 10 mg versus combination therapy and mirabegron 50 mg versus combination therapy. The estimated sample sizes for a 2-sample proportions test were calculated by Pearson chi-square test. With a power of 80% and for obtaining a statistically significant (α=.05) difference between solifenacin 10 mg and combination therapy of solifenacin 5 mg and mirabegron 25 mg, the sample size was calculated by a 2-sample proportions test.

To obtain a power of 80% and with 2-sided statistical significance level of 5%, given the probability of complete response to solifenacin 10 mg is 32% (π_1_=0.32) and the probability of complete response to combination therapy of solifenacin 5 mg and mirabegron 25 mg is 57.5% (π_2_=0.575), the required sample size is 59 in each group (1A, 1B, 2A, 2B). The sample size included the expected children who will continue the initial dose. In total, the required sample size is 236 participants.

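### Withdrawal for low compliance or reactions ends study participation, and the exit visit shares the end-of-study slot, so some week-18 outcomes will be lost or taken early

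*Protocol article*

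**What the plan says.** All references are to the protocol article.

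- **Withdrawal of Participants and Criteria for Discontinuation of Study** lists grounds on which a child leaves the study, at any time. They include severe noncompliance as judged by the investigator, and adverse reactions that endanger the child, cannot be reconciled with continuing, "or are expected to influence the results of the study".
- **Strengths and Limitations** names compliance over 18 weeks as the main limitation and offers "early termination of children with severe compliance issues (as <50%) during the treatment period" as the remedy.
- **Procedures During Pharmacotherapy, Table 1** heads its last column "Visit 3: end of study or premature discontinuation". The column is placed at week 18 (day 126), and nothing is scheduled after it.
- **Visit 3** says that after premature discontinuation the child continues at the outpatient clinic, where an unblinded doctor decides further treatment. It describes no later DryPie.
- **Primary End Point** is "treatment response assessed by change from visit 2 to end of study", with no week named. **Statistical Analysis** describes the same change over the 18 weeks of drug treatment.
- **Conclusion** refers to criteria for stopping the assigned therapy, which is not the same event as leaving the study.

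**The concern.** Compliance and adverse reactions are observed after randomisation. Once the add-on has started at visit 2, the arms within each primary comparison (1A against 1B, 2A against 2B) take different regimens, and families know which one. Reactions, and the decision to leave because of them, may then differ by arm and may be related to response.

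A ground that refers to the expected effect on the results is the least suitable of these, because it makes a predicted influence on the trial's findings a reason to remove the child. As the schedule stands, removal also ends outcome collection. An unseen analysis plan can define analysis sets and rules for missing data, but it cannot recover week-18 diaries that were never collected.

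What is at stake is whether the comparison at week 18 is made in the groups that were randomised, with the outcome measured at the same time in each.

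**Working it through.** **1. The plan's own figure.** Inputs from Sample Size: 15% complete response to low-dose monotherapy; among the remaining 85%, 20% on high-dose monotherapy and 50% on combination; two-sided alpha 0.05; power 80%.

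- Monotherapy arm: 0.15 + 0.85 × 0.20 = 0.32. Combination arm: 0.15 + 0.85 × 0.50 = 0.575. Mean: 0.4475.
- n = [1.960 √(2 × 0.4475 × 0.5525) + 0.842 √(0.32 × 0.68 + 0.575 × 0.425)]² / 0.255² = 58.5, rounded up to 59 per group and 236 in total.

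This reproduces the stated size. Power at 59 per group is 80.3%, and no allowance for withdrawal is stated, so there is no reserve.

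**2. What happens to a child who leaves early.** The cases follow from the schedule.

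- Leaves at or before visit 2: there is no value after the add-on, so no primary change.
- Leaves after visit 2 and the exit diary is used: the child is kept but measured before week 18.
- Leaves after visit 2 and the exit diary is not used: the child is lost.

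The last two are alternatives for any one child.

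**3. When each ground can act.** Tablets are counted at visits 2 and 3 only, so the count-based 50% threshold can stop a child early only at visit 2. Up to then 1A and 1B have had the same drug and dose, as have 2A and 2B. Withdrawal for reactions after the add-on is the stronger route to imbalance.

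**4. Possible size if withdrawn children were excluded.** The removal rates are assumptions, since the document gives none. Take 59 per arm, a true rate of 32% in both arms, and all removed children noncomplete responders. If a share a is removed, the observed rate is 0.32 / (1 − a) in 59(1 − a) children.

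- 5% v 15% removed: 0.32/0.95 = 33.7%, 0.32/0.85 = 37.6%, shift 4.0 points.
- 5% v 20% removed: 33.7% v 0.32/0.80 = 40.0%, shift 6.3 points.
- Equal removal: no shift under the null.

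The rejection rate is 1 − Φ[(1.960 SE₀ − d)/SE₁] + Φ[(−1.960 SE₀ − d)/SE₁], where d is the shift, SE₀ the pooled and SE₁ the unpooled standard error. For 5% v 15%, SE₀ = 0.0930 and SE₁ = 0.0931, which gives 7.1%. For 5% v 20% it is 10.2%. The nominal level is 5%.

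**5. Direction under the planned effect** (true difference 57.5 − 32 = 25.5 points), same assumptions.

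- 5% removed from monotherapy, 15% from combination: 0.575/0.85 − 0.32/0.95 = 67.6% − 33.7% = 34.0 points (before rounding the rates).
- 15% from monotherapy, 5% from combination: 0.575/0.95 − 0.32/0.85 = 60.5% − 37.6% = 22.9 points.

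**6. Loss without bias.** If children were lost at random, power would fall from 80.3% to 76.0% at 10% and 70.9% at 20%.

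**The case against.** The strongest reply is that the article names no analysis set and no rule for missing data, and that an article commonly leaves both to documents not shown here. This stands. A reader might infer that the primary comparison is selected on outcome. The text does not support that: the rules select on compliance and reactions, any link with response is an inference, and nowhere are withdrawn children said to be left out of the analysis.

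A reader might also infer that a child who stops soon after visit 2 and is dry that week is scored as a week-18 responder. No section says that an exit diary replaces the week-18 value, and Statistical Analysis points to 18 weeks. The fair statement is that the end point leaves this open.

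Three further points narrow the matter.

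- The count-based compliance threshold acts before the compared arms diverge, so alone it has little scope to unbalance them.
- Visit 2 allows a return to the initial dose level for side effects and similar problems without leaving the study. This should reduce withdrawals after the add-on.
- The investigator who judges noncompliance is blinded. The Conclusion expects fewer side effects on low-dose combination; on that premise removals would fall more on high-dose monotherapy, and bias could run against the trial's hypothesis.

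These points limit the likely size and leave the direction unknown. They do not supply the missing week-18 diary. Blinding does not make reaction rates equal, and the reaction ground applies at any time, including after the add-on.

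**Conclusion.** The point holds as a fault in the withdrawal and visit rules, not as a demonstrated bias. As written, children leave the study for post-randomisation reasons, the exit visit takes the end-of-study slot, and the primary end point is not fixed at week 18. Week-18 outcomes will be missing or early for some children, possibly unequally between arms.

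The size is unknown. The shift of about 4 to 6 points and the type I error of about 7% to 10% hold only if 5% v 15% to 20% are removed, all are noncomplete responders and all are excluded. With equal removal there is no shift under the null. The change is inexpensive and reduces the risk of bias, so it is worth making.

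**What to change.** - Reconcile Withdrawal of Participants, Strengths and Limitations, and Conclusion on whether each criterion stops the allocated therapy or ends participation in the study.
- Whatever the reason treatment stops, collect the 7-day DryPie at week 18 from every randomised child unless consent is withdrawn. Neither low compliance nor an expected influence on the results should end outcome collection.
- Name week 18 in the primary end point and separate the premature-discontinuation visit from it in Table 1, so that an early-exit diary is not taken as the week-18 value.
- Compare children in their allocated arm, and use compliance only in a supplementary analysis.

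When treatment itself should stop is a clinical decision and is not addressed here. How any week-18 values still missing are handled is a choice for the analysis plan.

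The cost is protocol wording and one diary week from children who stop. The estimate will include poor compliance and may be less favourable. The article reports 75 of 236 children included by April 2025, so 236 − 75 = 161 were still to be recruited then, and most of the data could still benefit.

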### Conclusion

If the low dose of combination therapy is superior to the high dose of monotherapy, children with DUI will benefit significantly from the new treatment in terms of shorter treatment periods, fewer side effects, and possibly a better quality of life. This trial has the potential to optimize the medical treatment approach, shorten the treatment period, diminish the side effects, and minimize unnecessary medical expenses. Due to predefined criteria for discontinuation of the allocated therapy, we expect the risk of treatment failure to be minimal. The results are expected to influence the treatment strategy of children with DUI worldwide.

## Appendix

Multimedia Appendix 1 CONSORT (Consolidated Standards of Reporting Trials) checklist.

## Abbreviations

AE: adverse event
CONSORT: Consolidated Standards of Reporting Trials
DUI: daytime urinary incontinence
OAB: overactive bladder
PinQ: pediatric incontinence questionnaire
PVR: postvoid residual
REDCap: research electronic data capture
SAE: serious adverse event
SUSAR: suspected unexpected serious adverse reaction
VAS: Visual Analog Scale
WHO-5: World Health Organization-Five Well-Being Index
